### **3.5. Sample size calculation**

Calculation of the number of clinical study subjects: As this study is an investigator-initiated clinical trial, the sample size was determined by referencing existing similar studies and clinical experience..

- 1) Level of significance,  $\alpha=0.05$ (two-tailed test)
- 2) Type II error ( $\beta$ ) is set at 0.2, making the power of the test 80%.
- 3) There is no existing study comparing Korean Chuna therapy and usual care for TMJ-related conditions in Korea. Therefore, based on clinical experience and manual therapy studies in China 1-3), the effect size for comparing the mean differences in pain VAS between the two groups is assumed to be at least medium (effect size = 0.7).
- 4) G\*Power 3.1.7 is used to calculate the sample size.

Assuming an effect size of 0.7, 34 subjects per group (a total of 68 subjects) are required. However, since the main analysis will be performed using ANCOVA, adjusting for baseline outcome values, and assuming a correlation value of 0.3 between baseline and the primary endpoint, the sample size is calculated as  $(1 - 0.3 * 0.3) * 68$ , resulting in 62 subjects. Considering a 30% dropout rate during the study, a total of 80 subjects will be recruited, with 40 subjects per group.

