| Number of participants | A total of 80 participants (considering a dropout rate of 30%), with 40 participants in each group. Patient recruitment will be conducted competitively and will continue until the total number of participants is reached.                                                                                                                                                                                                                                                                                                                                                                                                                                                                                                                                                                                                                                                                                                                                                                                                                                                                                                    |
| Objective              | This study aims to evaluate the effectiveness and cost-effectiveness of Chuna manual therapy in patients with chronic temporomandibular joint (TMJ) pain.                                                                                                                                                                                                                                                                                                                                                                                                                                                                                                                                                                                                                                                                                                                                                                                                                                                                                                                                                                       |

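### Recruiting 80 with 30% dropout leaves 56 participants, not the 62 the plan requires, so the stated 80% power is not met on the plan's own assumptions

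*Protocol*

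**What the plan says.** Section 3.5 (Sample size calculation) of the protocol builds the number in three steps.

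1. For a two-sided 5% test with 80% power, the between-group effect on pain VAS "is assumed to be at least medium (effect size = 0.7"), from which "34 subjects per group (a total of 68 subjects) are required".
2. Because the main analysis is a baseline-adjusted ANCOVA, and "assuming a correlation value of 0.3 between baseline and the primary endpoint", the 68 is multiplied by 1 − 0.3², giving 62.
3. Attrition is then added: "Considering a 30% dropout rate during the study, a total of 80 subjects will be recruited, with 40 subjects per group".

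The Summary of Protocol (Number of participants) repeats the pairing of 80 recruits with 30% dropout. Sections 5.1 and 5.2.1 carry 40 per group forward. Section 3.4 says that participants who discontinue are not replaced. Section 6.1 places the primary endpoint, VAS, at week 5.

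**The concern.** An attrition allowance has to leave the required number after losses, so the required number is divided by the proportion retained. Multiplying it by one plus the dropout rate gives too few, and the gap grows with the rate. At 30% the two forms differ by about 8 participants here (88.6 against 80.6).

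The protocol therefore asserts three things that cannot all be true: 80 recruited, 30% lost, and 80% power at an effect size of 0.7. Power is the figure a reader turns to when a trial finds no difference. A reader of a null result would credit this trial with more power than its own assumptions give it. Because dropouts are not replaced, nothing later in the protocol restores the number.

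**Working it through.** **Inputs, all from protocol section 3.5:** two-sided α = 0.05; power 80%; standardised effect d = 0.7; baseline–endpoint correlation r = 0.3; dropout 30%; 80 recruited, 1:1.

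**Step 1, unadjusted size.** Two-sample t-test, noncentral t distribution, d = 0.7:
- 33 per group: power 79.97%, just short of 80%
- 34 per group: power 81.2%

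So 34 per group and 68 in total reproduce.

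**Step 2, ANCOVA reduction.** (1 − r²) × 68 = (1 − 0.09) × 68 = 0.91 × 68 = 61.88, rounded up to 62 (31 per group). This reproduces. To confirm that 62 is adequate, baseline adjustment shrinks the residual SD by √(1 − r²), so the effective effect size is 0.7 / √0.91 = 0.734. With noncentrality 0.734 × √(n/2) and 2n − 3 degrees of freedom, n = 31 per group gives 81.1% power.

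**Step 3, dropout.**
- Dividing by the proportion retained: 62 / 0.7 = 88.6, so 89, or 90 for equal groups. Check: 90 × 0.7 = 63, which is at least 62.
- Multiplying by one plus the rate: 62 × 1.3 = 80.6. This is the standard variant that lands near the stated 80, and it needs rounding down to get there.
- Retained from the stated 80: 80 × 0.7 = 56, or 28 per group. Shortfall: 62 − 56 = 6.
- Dropout at which 80 still leaves 62: 1 − 62/80 = 22.5%.

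**Step 4, power with 80 recruited.** Same ANCOVA formula, d = 0.7, r = 0.3:

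| Loss | Remaining | Power |
|---|---|---|
| 20% | 64 | 82.3% |
| 22.5% | 62 | 81.1% |
| 25% | 60 | 79.8% |
| 30% | 56 | 76.9% |

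At 28 per group the effect detectable with 80% power is d = 0.73. A normal approximation gives 78.4% at 28 per group, also below 80%. The t-based figure is preferred because the t-based method reproduces the protocol's 34 per group; the normal approximation gives 33.

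**The case against.** Five points can be made on the other side.

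- **Timing.** The 30% refers to the whole study, which runs to month 6, while the primary endpoint is at week 5. Loss by week 5 cannot exceed the study-long loss and may be lower; at 22.5% or less the 62 is met. This is fair, and it makes 76.9% the lower end of the range. But section 3.5 applies 30% to the primary-endpoint calculation and gives no week-5 rate, so the stated justification still fails.
- **Analysis set.** Section 6.3.2 analyses everyone who received at least one treatment, with multiple imputation, and section 3.4 allows follow-up after discontinuation with consent. VAS readings from weeks 1 to 4 could inform the imputation. So 76.9% treats every dropout as contributing nothing, which is somewhat pessimistic. Imputation does not in general restore the information lost with a missing week-5 value, however, and the dropout allowance in section 3.5 itself counts lost participants as lost to power.
- **Size.** The loss is about 3 points, on an effect size that is itself approximate. The result also depends on the assumed correlation: at 28 per group, power is 80.1% if r = 0.4 and 84.4% if r = 0.5, both illustrative values. The modest size stands, but the plan chose r = 0.3.
- **Mechanism.** That 62 × 1.3 was used is an inference, since no formula is printed. Agreed; the contradiction rests only on 80 × 0.7 being less than 62.
- **Tolerance.** The 62 carries a little slack. Power reaches 80.4% with 61 (31 + 30), so the tolerable loss for 80% power itself is 1 − 61/80 = 23.75%. This is correct, and still well below 30%.

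**Conclusion.** The concern holds. The first two steps of the calculation reproduce exactly; the third does not. On the plan's own figures, 80 recruited with 30% dropout leaves 56, which is 6 below the 62 it requires. Power is then 76.9% instead of 80%, or equivalently the detectable effect is 0.73 instead of 0.70. These power figures assume d = 0.7, r = 0.3, equal loss in both groups, all 30% lost by week 5, and no information recovered from those lost. If week-5 loss is smaller, power is higher, and at 22.5% loss the 62 is preserved. The practical loss is modest, but a headline statement of the protocol is arithmetically wrong and nothing elsewhere in the document corrects it.

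**What to change.** Amend section 3.5 and the Summary of Protocol together, in one of two ways:

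- keep 80 and change the attrition statement: 80 recruited retains the required 62 at up to 22.5% dropout, with a sentence on why loss by week 5 is expected to stay within that; or
- keep 80 and 30%, and change the power statement: 56 are expected to remain, giving about 77% power at d = 0.7 (detectable effect 0.73 at 80% power).

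Either version should show the inflation step explicitly. Both are wording changes that need no extra participants; their cost is a slightly less favourable stated power or tolerated dropout. If the sponsor prefers to keep both 30% dropout and 80% power, the consistent number is 90 (45 per group). That means 10 more participants and matching changes to the 40-per-group figures in sections 5.1 and 5.2.1.

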## **4. Research Period**

18 months from IRB approval date

## **5. Method**

### **5.1. Design**

The study design is a 2-arm parallel multicenter RCT (Kyung Hee University Hospital of Korean Medicine, Gangdong, Jaseng Hospital of Korean Medicine (Gangnam), Daejeon Jaseng Hospital of Korean Medicine, Bucheon Jaseng Hospital of Korean Medicine, Haeundae Jaseng Hospital of Korean Medicine). Study participants will receive outpatient treatment for a total of 4 weeks. After screening at the initial visit, participants who meet the inclusion/exclusion criteria will be randomly assigned to either the Chuna manual therapy group (40 participants) or the usual care group (40 participants). Treatment for temporomandibular joint (TMJ) pain disorders will be administered according to the developed clinical study protocol.

For the economic evaluation study, cost data collection and utility assessment for estimating QALY (Quality Adjusted Life Year) will be conducted. During the clinical study period, quality of life will be assessed using EQ-5D, EQ-VAS, and SF-12 measurement tools at Visits 2, 10, and 12. Various costs will be assessed using developed survey items at the first visit of each week. Additionally, a separate follow-up survey will be conducted until 6 months (Visit 12) after clinical study enrollment. The survey will be conducted through face-to-face interviews, telephone interviews, or distributed questionnaires, measuring healthcare utilization and quality of life.

### **5.2. Random allocation and blinding**

#### **5.2.1. Random allocation**

When subjects who have voluntarily signed the informed consent form are reviewed and determined to meet the inclusion and exclusion criteria, and thus are deemed suitable for the clinical study, they will be assigned to one

of two groups using a block randomization method. This method will be implemented by a statistician using nQuery Advisor 7.0 (or SAS 9.0 or SPSS 21.0), with an equal number of patients (40 each) allocated to both groups. The block size will remain undisclosed to the personnel conducting patient recruitment and group allocation.

Random assignment will occur based on patient registration at each of the five institutions, without stratification by institution. Patient recruitment will follow a competitive enrollment process at each hospital and will continue until the total number of patients is achieved. Participants will be assigned an identification code (Randomized Number) in the order of recruitment according to the random allocation details. The results of the central randomization will be communicated to each institution conducting the clinical study, and treatment will proceed accordingly in each group.

#### 5.2.2. Allocation concealment and blinding

After providing patients with a thorough explanation of the clinical study, those who meet the inclusion and exclusion criteria and sign the written consent form will be assigned to groups using opaque, sealed envelopes. Since it is not feasible to blind the practitioners and participants in this study, only the assessors will be blinded. Assessor, who do not participate in the procedures and are blinded to group assignments, will conduct assessments in a separate area after the procedures are completed. These evaluations will be performed by clinical research coordinator or residents.

### 5.3. Pre-Clinical Study Evaluation

#### 5.3.1. Patient Consent, Screening Number Assignment, and Demographic Survey

Before the clinical study begins, the purpose and details of the study will be thoroughly explained to the subjects. Written consent will be obtained, and screening numbers will be assigned in the order of receiving the written consents. Afterward, demographic information will be collected.

#### 5.3.2. Medical History and Medication History Investigation

The subject's medical history and medication history will be thoroughly investigated and recorded through interviews and review of past medical records. The details to be included are as follows:

- Surgical history
- Past medical history and comorbidities, treatment history for heart disease and gastrointestinal diseases
- Any adverse reactions to previous pharmacopuncture treatment and general treatments (medication, physical therapy)
- Current medical history
- Evaluation of inclusion/exclusion criteria compliance
- Other medication treatments and treatment history
- Pre-clinical study cost investigation: Investigate the treatment costs related to the disease incurred before participating in the clinical study since the onset of the disease
- Quality of life measurement: Measure the patient's quality of life before participating in the clinical study using tools such as EQ-5D-5L.

#### 5.3.3. RDC/TMD Examination

- The RDC/TMD (Research Diagnostic Criteria for Temporomandibular Disorders) diagnostic tool was proposed by Samuel F. Dworkin and Linda LeResche in 1992 and has been widely used in studies as a diagnostic tool for temporomandibular disorders. According to this tool, temporomandibular disorders can be classified into three categories: myofascial pain, disc displacement, and joint problems. Pain disorders fall into the myofascial pain group and part of the joint problem group. Additionally, the diagnostic and examination process includes a multi-faceted analysis of temporomandibular joint issues, such as mouth opening range, active and passive ROM, degree of pain and discomfort, and other symptoms.

- Moreover, there is a translated version of RDC/TMD by Korean researchers, approved by the international RDC/TMD consortium as validated data suitable for research purposes. In this study, patients confirmed to have temporomandibular joint problems with pain after the RDC/TMD examination will be targeted. The RDC/TMD diagnostic criteria consist of two axes. Axis I, which classifies symptoms, includes three groups: Group I, II, and III. Of these, Groups I and III use pain as an indicator. Group I a/b includes myofascial pain (without mouth opening limitation, a; with mouth opening limitation, b), and Group III a/b includes arthralgia and osteoarthritis, respectively.

### 5.4. Intervention

#### 5.4.1. Chuna manual therapy

1) Standardization of CMT for treatment of TMD patients.

CMT will be standardized according to the content of this protocol to remove any bias due to the techniques used

and the intensity of the performance.

2) Preparation for the procedure

The participant is sitting on a chair or lying on a table. A KMD washes hands with cleansing.

3) CMT procedure

CMT techniques: 6 techniques are selected as follows by referring to the textbook of Chuna manual medicine [11] and literature on the effect of manual therapy on the cervical spine for TMD patients. The intensity of the distraction technique (two of the techniques for cervical spine) will be set not to make participants feel uncomfortable, but to mobilize them as far as the limits of the passive range of motion. After conducting all of the techniques, the participants will spend 10 min at rest, to observe any adverse events.

4) Frequency and duration of CMT 10) Frequency: a total of eight times over 4 weeks (two times a week) 11) Time duration of a performance: 20 min total (10 min for CMT, and 10 min for rest after treatment)

|                        |                                                               |
|------------------------|---------------------------------------------------------------|
| CMT for TMJ            | Sitting TMJ distraction with thumb technique                  |
|                        | Sitting lateral pterygoid pushing with index finger technique |
|                        | Sitting TMJ manipulation with thumb technique                 |
| CMT for cervical spine | Supine cervical spine distraction technique                   |
|                        | Supine cervical spine JS distraction manipulation technique   |
|                        | Supine cervical spine manipulation technique                  |

5.4.2. Usual care

- Physical therapies that were proven to alleviate TMD symptoms include thermotherapy, ultrasound therapy, TENS, ICT, etc. In this study, it will be limited to one of thermotherapy, ultrasound therapy, TENS or ICT for the UC group, and will be applied to the area around the neck or the TMJ. Reduction of pain, anti-inflammation, muscle activation, healing, and regeneration of tissue are the mechanisms reported thus far for these therapies [21].

- Frequency and duration of UC: a total of eight times over 4 weeks (two times a week), total 20 min (10 min for the treatment and 10 min for rest after treatment)

5.4.3. Education

- Education on TMD will be conducted for the participants of both groups. It covers the causes, prevention, treatment, management, and self-stretching for TMD, using specially assembled materials.

## 5.5. Items to be investigated and Methods

### 5.5.1. Demographic Data / Other Pre-Treatment Characteristics

For patients who meet the inclusion criteria, the following data will be collected:

- Gender
- Date of birth
- Age (in full years)
- Height, weight
- Vital signs: body temperature, blood pressure, pulse rate
- Medical history: During the first visit, the patient's medical history will be thoroughly investigated and recorded through a questionnaire and review of past medical records. This should include past illnesses and comorbidities, history of heart and gastrointestinal diseases, surgical history, current illnesses, and any other medications or treatments received.
- Physical examination: Significant findings from the first visit's examination will be recorded in the physical examination section of the case report form. If any significant physical findings meeting the definition of adverse events are discovered after the start of the study procedure, they will be recorded in the adverse event case report form. However, any undesirable physical symptoms identified before the start of the study procedure should be added to the current illness investigation section.
- 

### 5.5.2. Concomitant Therapy

During the treatment period (week 1-4), medications and treatments from other medical institutions for temporomandibular joint (TMJ) disorders are not allowed. These treatments are permitted during the observation period. Any treatments received during the follow-up period should be recorded at the final visit.

### 5.5.3. Prohibited Medications

- From study registration until the primary endpoint at week 5 (visit 10), all direct treatments aimed at relieving TMJ pain (e.g., medications, surgeries, other types of acupuncture, and physical therapy) are prohibited for both the clinical study group and the control group. No treatment restrictions are applied during the observation period after the primary endpoint at week 5.

However, during the study period, rescue medication such as acetaminophen (e.g., Tylenol, Acetaminophen tab) will be allowed for all clinical study subjects up to a maximum of 4g per day, and the usage of this medication will be recorded through self-reporting.

#### 5.5.4. Subject Management During the Follow-Up Period After Treatment Completion

- Clinical study subjects who do not feel completely cured by the final visit or those who experience a recurrence of pain after the treatment completion visit will be allowed to receive treatment at a medical institution of their choice. The details of such treatments will be recorded during the follow-up visits.
- In preparation for any unexpected delayed adverse reactions, subjects will be allowed to seek medical care at any time under the researcher's instructions.

### 5.6. Imaging Examination Items

- The X-ray examination
- Anteroposterior (closed) and both lateral views (closed, open) X-rays will be performed.

## 6. Outcomes

### 6.1. Primary outcomes

#### Visual Analogue Scale (VAS) for TMJ pain

VAS will be evaluated on the 1st, 3rd, 5th, and 7th treatment visits (week 1–4) and 5 weeks, 3 months, and 6 months after allocation. The average TMJ pain for the past week will be investigated. The primary endpoint is VAS at 5 weeks after allocation (a week after the last treatment). The far left end of a 100 mm scale line means “no pain” and the far right end means “the worst pain imaginable.” It is the most frequently used way to measure the pain severity. A participant puts a mark on the line, which approximates his/her own pain for the past week. If a participant complains of different pain levels on each TMJ, the more severe side will be recorded.

### 6.2. Secondary outcomes

#### Numeric Rating Scale (NRS) for TMJ pain and bothersomeness.

This outcome will be checked at screening, at every treatment visit, and 5 weeks, 3 months, and 6 months after allocation. Participants will be asked to select one digit that shows the level of TMJ pain and bothersomeness for the past week (0 means no pain or bothersomeness, and 10 the most severe degree).

#### Range of Motion (ROM) of the TMJ

The ROM of the TMJ will be evaluated at screening, and at the 1st, 3rd, 5th, 7th treatment visits (week 1–4) and after 5 weeks. Active maximum mouth opening without pain, protrusion, and each lateral movement of the mandible will be measured using the Range of Motion Ruler (Therabite, Sweden). Participants will be asked to open the mouth as much as possible without any pain, to slightly open the mouth and protrude the mandible as much as possible and to slightly open the mouth and move the jaw as much as possible to each side. The measuring process will be concretely conducted in accordance with the specifications for clinical examination provided by the international RDC/TMD consortium.

